# Anaesthesia Choice for Creation of Arteriovenous Fistula (ACCess) study protocol : a randomised controlled trial comparing primary unassisted patency at 1 year of primary arteriovenous fistulae created under regional compared to local anaesthesia

**DOI:** 10.1136/bmjopen-2021-052188

**Published:** 2021-12-22

**Keywords:** adult anaesthesia, end-stage renal failure, vascular surgery, transplant surgery

## Abstract

**Introduction:**

Arteriovenous fistulae (AVF) are the ‘gold standard’ vascular access for haemodialysis. Universal usage is limited, however, by a high early failure rate. Several small, single-centre studies have demonstrated better early patency rates for AVF created under regional anaesthesia (RA) compared with local anaesthesia (LA). The mechanistic hypothesis is that the sympathetic blockade associated with RA causes vasodilatation and increased blood flow through the new AVF. Despite this, considerable variation in practice exists in the UK. A high-quality, adequately powered, multicentre randomised controlled trial (RCT) is required to definitively inform practice.

**Methods and analysis:**

The Anaesthesia Choice for Creation of Arteriovenous Fistula (ACCess) study is a multicentre, observer-blinded RCT comparing primary radiocephalic/brachiocephalic AVF created under regional versus LA. The primary outcome is primary unassisted AVF patency at 1 year. Access-specific (eg, stenosis/thrombosis), patient-specific (including health-related quality of life) and safety secondary outcomes will be evaluated. Health economic analysis will also be undertaken.

**Ethics and dissemination:**

The ACCess study has been approved by the West of Scotland Research and ethics committee number 3 (20/WS/0178). Results will be published in open-access peer-reviewed journals within 12 months of completion of the trial. We will also present our findings at key national and international renal and anaesthetic meetings, and support dissemination of trial outcomes via renal patient groups.

**Trial registration number:**

ISRCTN14153938.

**Sponsor:**

NHS Greater Glasgow and Clyde GN19RE456, Protocol V.1.3 (8 May 2021), REC/IRAS ID: 290482.

Strengths and limitations of this studyThis is a prospective, multicentre, randomised, observer-blinded trial designed to examine whether primary radiocephalic/brachiocephalic arteriovenous fistulae created under regional anaesthesia (RA) rather than local anaesthesia (LA) have better 1-year primary unassisted functional patency.With 566 participants, this will be the largest trial to date comparing RA to LA and will address criticisms of previous smaller, single-centre randomised trials.An associated cost-effectiveness analysis will provide sufficient evidence to guide practice and policy.The main limitation of this study is that in predialysis patients, the primary endpoint uses surrogate markers of fistula patency (clinical assessment and ultrasound scan criteria) rather than successful use of the fistula for haemodialysis.

## Introduction

The incidence of kidney failure requiring kidney replacement therapy has increased substantially over the last 30 years, and over 25 000 people in the UK are currently treated with maintenance haemodialysis (HD).^1^ Kidney disease has a significant impact on both longevity and quality of life and places considerable demand on healthcare resources.^2^ Vascular access is ‘a major modifiable risk factor’ in terms of patient experience and outcome on HD, with arteriovenous fistulae (AVF) being the preferred mode of vascular access.^3^ Patients dialysing via AVF experience less infective and thrombotic complications, and are three times less likely to be admitted to the hospital than their counterparts with central venous catheters (CVCs).^3^ Such frequent hospitalisations have a negative impact on health-related quality of life (HRQoL).^4^ Furthermore, there are observational data demonstrating superior survival in patients successfully dialysing via AVF compared with those using CVCs or prosthetic arteriovenous grafts (AVGs) for dialysis.^5^

Despite these benefits, universal adoption of AVF remains suboptimal. The most recent UK Renal Registry (UKRR) Multisite Dialysis Access Audit highlighted that nearly 80% of dialysis units in England, Wales and Northern Ireland still fail to achieve renal association targets, which recommend that 60% of incident patients receive HD via AVF or AVGs.^6 7^ One principal obstacle to the widespread use of AVF is ‘failure to mature’, with early failure rates approaching 50%.^8 9^ Any intervention that improved AVF maturation should confer significant benefit to patient health and well-being, reduce surgical workload and deliver cost savings.

Anaesthetic technique is one such factor believed to influence AVF maturation and outcome. Regional anaesthesia (RA), unlike local anaesthesia (LA), generates a sympathetic blockade. The mechanistic hypothesis is this sympathetic blockade results in vasodilatation, improved tissue oxygenation and increased blood flow through the new fistula, therefore reducing early thrombosis.^8 10^ Several studies have demonstrated superior short-term patency rates of AVF created under brachial plexus block (BPB) compared with LA.^8 11^ In the only randomised controlled trial (RCT) to date with prolonged follow-up, RA improved both early and 1-year functional AVF patency compared with LA.^12^ A concomitant health economic analysis using HRQoL data extrapolated from the literature established net cost savings at 1 year and an incremental cost-effectiveness ratio (ICER) of approximately £12 900 per quality-adjusted life year (QALY) gained over a 5-year time horizon with RA.

Both European Society for Vascular Surgery and European Renal Association guidelines suggest considering using RA for all primary AVF.^13 14^ The Kidney Disease Outcomes Quality Initiative Vascular Access guidelines disagree, stating choice of anaesthesia should be based on operator discretion.^15^ Such disparity regarding the choice of anaesthesia for AVF creation is reflected across UK centres, with significant variation in practice.^16^ While this is in part due to a lack of anaesthetic availability or capability, the failure to modify local practices perhaps also reflects the lack of strong evidence. All RCTs to date have been single-centre, with some suffering from methodological flaws.^11^ Further, more robust, health economics analysis is required to establish whether any potential durable clinical benefit could be offset against the longer procedural times, need for a skilled anaesthetist and the additional upfront costs associated with RA. Only a definitive, adequately powered, multicentre RCT with associated cost-effectiveness analysis will provide sufficient evidence to change practice and policy. The Anaesthesia Choice for Creation of Arteriovenous Fistula (ACCess) trial aims to address this issue, with the primary objective being to determine whether or not the sympathetic blockade associated with regional compared with LA translates into clinical improvements in long-term functional fistula patency.

## Methods and analysis

The ACCess study is a multicentre, observer-blinded, parallel group, superiority RCT with an internal pilot and embedded process evaluation study comparing patients undergoing primary radiocephalic fistula (RCF) or brachiocephalic fistula (BCF) creation under RA versus LA. The primary outcome is unassisted functional AVF patency at 1 year. The participant timeline is outlined in figure 1.

**Figure 1 F1:**
[figure not shown]
Participant timeline. AVF, arteriovenous fistula; HRQoL, health-related quality of life; LA, local anaesthesia; RA, regional anaesthesia; US, ultrasound.

### Participants

Patients will be recruited from high-volume (>150 cases per year) and medium-volume (>50 cases per year) UK centres providing vascular access for HD.

### Recruitment

Potentially eligible participants will be identified from vascular access and/or ‘predialysis’ (low-clearance) clinics and theatre waiting lists by the clinical team. A vein mapping ultrasound (US) will be performed to ensure minimum vessel characteristics. We anticipate 12–20 centres recruiting an average of two patients/centre/month. Recruitment is due to commence May 2021 and is anticipated to take 2 years. Preliminary results are expected late 2024.

### Inclusion criteria

Inclusion criteria are outlined in box 1.

Box 1Inclusion and exclusion criteriaInclusion criteriaAll adult patients (≥18 years old) with kidney failure requiring kidney replacement therapy or chronic kidney disease stage IV or V referred for primary radiocephalic fistula or brachiocephalic fistula creation.Exclusion criteriaGeneralPatients unable or unwilling to provide informed consent.Patient preference for general or alternative anaesthesia.Active infection at surgical or anaesthetic site.Access specificPrevious ipsilateral AVF creation (a previous attempt at distal AVF creation which fails immediately is not considered a contraindication, but any distal access which has previously run sufficiently to mature the outflow vein or proximal revision of an existing AVF is considered a contraindication).Known ipsilateral cephalic arch or central venous stenosis (even if previously treated).USS evidence of stenosis in inflow artery.Radial or brachial artery of <1.8 mm diameter and/or cephalic vein of <2 mm at the wrist or <3 mm at the elbow (with tourniquet) on preoperative USS.^29^
Contraindications to anaesthetic agents/ techniqueAllergy to local anaesthesia or any excipient agents.Acquired or inherited coagulopathy (including warfarin/heparin/novel oral anticoagulant use where it has not been possible to stop the anticoagulation in anticipation of surgery) and/or platelets of <75 or International Normalised Ratio (INR) of >1.4.^30^
Significant pre-existing neurological disorder affecting the upper limb.Weight of <45 kg.

### Exclusion criteria

Exclusion criteria are outlined in box 1.

### Allocation

A central randomisation facility (interactive web response system) at the Robertson Centre for Biostatistics (RCB), University of Glasgow, will randomise patients 1:1 to the intervention group (RA) or the comparator group (LA). The randomisation list will be created by a computer-generated program using a method of permuted blocks stratified by centre, dialysis status (predialysis/HD) and site of AVF (RCF/BCF). Randomisation will take place at a patient, not centre, level to minimise bias from variation in surgical and dialysis practice. The randomisation list, the program that generated it and the random seed used will be stored in a secure network location, accessible only to those responsible for provision of the randomisation system. Clinicians responsible for delivering the perioperative care will perform the web-based randomisation.

### Intervention

The choice of anaesthetic agents is influenced largely by the successful use of these combinations in a previous study,^8^ the ready availability of these drugs within the UK, acceptability to collaborating centres, and the ability of the combination to provide both rapid onset and prolonged duration of block.^17^

#### Interventional arm: RA

An US-guided supraclavicular or axillary BPB will be administered by a consultant anaesthetist trained in RA or a trainee practising under direct supervision. The supraclavicular approach will be considered first-line, unless the anatomy or patient risk profile is unfavourable. In patients on antiplatelets or other anticoagulants, the choice between supraclavicular and axillary block will be at the anaesthetist’s discretion, taking into account ‘compressibility, vascularity and consequences of bleeding’.^18^ Where pulmonary disease is present, an axillary nerve block eliminates the risk of pneumothorax or temporary phrenic nerve paralysis.

A 1:1 mixture of 0.5% L-bupivacaine and 1% lidocaine, mixed with epinephrine to 1 in 400 000 final concentration, will be used (online supplemental appendix 1). Maximum dose limits are 2 mg/kg for bupivacaine and 7 mg/kg for lidocaine with epinephrine, recognising the effects are additive. The volume of LA injected must account for patient weight and maximum dose limits while considering the need for LA supplementation. In a study where the median patient weight was 66 kg, the ED_95_ (effective volume in 95% of patients) for supraclavicular blocks was 27 mL.^19^ A minimum volume of 25 mL must be injected for patients over 60 kg. This is reduced to 20 mL for patients weighing 51–60 kg and 15 mL in patients weighing <45 kg (online supplemental appendix 1). A suggested supraclavicular technique involves depositing a minimum of 25% of LA in the ‘corner pocket’ between the first rib and the subclavian artery and the remainder posterolateral to the plexus, avoiding deliberate intracluster injection.^20^ For axillary blocks, the same minimum volumes must be used, targeting 25% of the LA to the musculocutaneous nerve, with the remainder deposited around the ulnar, median and radial nerves, as well as the cutaneous nerves of the arm and forearm if visualised.

10.1136/bmjopen-2021-052188.supp1Supplementary data

Sensory and motor block of musculocutaneous, median, radial and ulnar nerves will be recorded every 5 min using a validated 3-point scale.^21^ Sensory blockade of the medial cutaneous nerve of the forearm and arm will also be recorded. Measurements will be continued until either sensory block is adequate or 30 min has elapsed, at which point the block may be supplemented by targeted US-guided axillary or midhumeral injection as appropriate.

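### The 15 mL minimum block volume is attached to patients under 45 kg, whom the trial excludes, so eligible patients from 45 kg to below 51 kg have no stated minimum

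*Protocol article*

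**What the plan says.** The section on the interventional arm (RA) in the protocol article prescribes the block mixture as "A 1:1 mixture of 0.5% L-bupivacaine and 1% lidocaine, mixed with epinephrine to 1 in 400 000 final concentration". It caps the dose: "Maximum dose limits are 2 mg/kg for bupivacaine and 7 mg/kg for lidocaine with epinephrine, recognising the effects are additive". It then sets lower limits on the injected volume by body weight. The first is "A minimum volume of 25 mL must be injected for patients over 60 kg". The next sentence, which ends with a reference to online supplemental appendix 1, gives the two lower bands: "This is reduced to 20 mL for patients weighing 51–60 kg and 15 mL in patients weighing <45 kg". For the alternative approach the section adds: "For axillary blocks, the same minimum volumes must be used".

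Box 1, under contraindications to anaesthetic agents or technique, lists as an exclusion "Weight of <45 kg".

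**The concern.** The lowest volume band and the weight exclusion use the same cut-off from the same side. A patient light enough for the 15 mL minimum is too light to enter the trial. A patient between the eligibility floor and the start of the 20 mL band has no minimum in the text.

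The minimum volume is part of what defines delivery of the experimental treatment, and the article words it as an obligation. A reader treating a 47 kg participant cannot tell from the article whether 15 mL, 20 mL or no floor applies. Adherence is also used elsewhere in the article: a per-protocol analysis is foreseen (Statistical analysis plan), the volume of anaesthetic agent is a secondary outcome (Box 2), and non-adherence in more than 20% of participants stops the trial at the pilot (Interim analysis and early termination criteria). For these patients the article offers no volume floor against which adherence could be judged.

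**Working it through.** No sample size, power or error rate is involved. The check is first logical, then a plausibility check of the likely intended rule.

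**Step 1. Eligibility against the printed bands.** Box 1 excludes weights below 45 kg, so eligible means 45 kg or more. Setting this beside the printed bands:

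| Weight | Eligible under Box 1 | Printed minimum volume |
|---|---|---|
| below 45 kg | no | 15 mL |
| 45 to below 51 kg | yes | none stated |
| 51–60 kg | yes | 20 mL |
| above 60 kg | yes | 25 mL |

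The 15 mL band and the eligible population share no weight. In whole kilograms the uncovered eligible weights are 45, 46, 47, 48, 49 and 50.

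**Step 2. The likely intended band.** Reading the last band as 45–50 kg starts it at the eligibility floor and ends it next to the 51–60 kg band. Every eligible whole-kilogram weight then has exactly one minimum. The volume per kilogram also runs on from the band above: 20/51 = 0.392 to 20/60 = 0.333 mL/kg in the middle band, and 15/45 = 0.333 to 15/50 = 0.300 mL/kg in the lowest.

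**Step 3. Is 15 mL permissible at 45–50 kg?** Mixing 0.5% L-bupivacaine (5 mg/mL) and 1% lidocaine (10 mg/mL) in equal parts gives 2.5 mg/mL and 5 mg/mL. So 15 mL holds 15 × 2.5 = 37.5 mg bupivacaine and 15 × 5 = 75 mg lidocaine.

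| Weight | Bupivacaine (limit 2 mg/kg) | Lidocaine (limit 7 mg/kg) |
|---|---|---|
| 45 kg | 37.5/45 = 0.83 mg/kg | 75/45 = 1.67 mg/kg |
| 50 kg | 37.5/50 = 0.75 mg/kg | 75/50 = 1.50 mg/kg |

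**Step 4. Allowing for additive effects.** The article calls the effects additive but gives no formula. Assume this means that the fractions of the two limits are summed: F = 2.5V/(2w) + 5V/(7w) = 1.964 × V/w, for volume V in mL and weight w in kg.

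- 15 mL at 45 kg: 0.417 + 0.238 = 0.655.
- 15 mL at 50 kg: 0.375 + 0.214 = 0.589.
- Setting F = 1, the ceiling is 45/1.964 = 22.9 mL at 45 kg and 50/1.964 = 25.5 mL at 50 kg.
- If a reader instead carried the 20 mL floor down to 45 kg: 20 × 1.964/45 = 0.873. This is still within the limit, but the margin left for supplementation falls from about 35% to about 13%.

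Steps 2 to 4 show only that the proposed reading is coherent and permissible. The contradiction itself rests on step 1.

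**The case against.** The strongest reply is that this is a slip in one sentence of a condensed article, and that the same sentence sends the reader to supplemental appendix 1, where the dosing table may be correct. Detail left to a fuller document is not missing. This limits the point but does not remove it: the article does not leave the band to the appendix, it prints one, and the printed band conflicts with the article's own eligibility criteria. If the appendix is right, the two disagree.

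A second reply is that the practical effect is slight. That stands. Sensory and motor block are recorded every 5 minutes until adequate or until 30 minutes have passed, when the block may be supplemented. There is an algorithm for failed blocks, and the oversight committees monitor their number. Blocks are given by a consultant trained in regional anaesthesia or a directly supervised trainee. These are the safeguards against too little anaesthetic. The maximum dose limits protect against the opposite error, too high a volume in a light patient, and are no answer to a missing floor.

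Third, 45–50 kg is an inference. A reversed inequality sign, or a slip for below 51 kg, would also explain the text. Each of these leads to 15 mL at the uncovered weights, so the doubt concerns the wording more than the dose. The certainty attaches to the contradiction, not to the replacement.

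**Conclusion.** The point holds: the lowest dosing band in the experimental arm is wrong as written. It applies to no eligible patient, and the article text gives no minimum from 45 kg to below 51 kg for either supraclavicular or axillary blocks. It should be fixed, but it is a minor correction. Sample size and the primary analysis do not depend on it, and no harm to patients is implied. How many participants fall in the gap cannot be estimated from the document.

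The contradiction needs no assumption. The replacement band assumes a misprint, and the 65% and 59% shares of the dose ceiling assume that additive means a sum of fractions. The conclusion covers this sentence only, since appendix 1 was not available.

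**What to change.** Check the dosing table in supplemental appendix 1, confirm the intended rule with the clinical leads, and correct the lowest band to 15 mL for patients weighing 45–50 kg. If weights are recorded unrounded, write 45 to <51 kg, so that no weight falls between bands. Every eligible weight then has exactly one minimum for both block approaches. If the appendix carries the same error, correct it too.

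The cost is one wording change and one table check, with no effect on sample size, analysis or timeline.

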#### Comparator arm: LA

A 1:1 mixture of 0.5% L-bupivacaine and 1% lidocaine will be infiltrated around the operative site by the operating surgeon. After 5 min, adequacy of anaesthesia will be tested by application of a painful stimulus and additional LA infiltration administered as required. Maximum dose limits of 2 mg/kg for bupivacaine and 3 mg/kg for lidocaine will be observed, recognising the effects are additive.

#### Management of a ‘failed block’ (or failure of LA)

A failed block will be defined as any block that, despite the targeted intervention described previously, requires additional supplementation with LA, analgesia, conversion to general anaesthesia or abandonment of surgery. The algorithm for failed block or ‘failed LA’ will be as follows:

Supplementation at surgical site with LA (1% lidocaine) up to maximum cumulative LA dosage.Intravenous sedation and analgesia at the discretion of the anaesthetist.General anaesthesia.Abandonment of procedure: decision to be made following discussion between operating surgeon and anaesthetist if deemed unsafe to proceed with general anaesthesia.

The Trial Steering Committee (TSC)/Independent Data Monitoring Committee (IDMC) will monitor the number of failed blocks for patient safety and quality assurance throughout the study.

### Fistula surgery

A standard approach to the vessels will be via a transverse incision at, or just below, the elbow crease for BCF and longitudinal or curvilinear incision at the wrist for RCF. The cephalic vein (or median cubital vein if suitable) will be dissected and skeletalised for a short length proximally and distally. Visible branches will ligated and divided. The vein will be divided, spatulated where appropriate and flushed with heparinised saline. The artery will be dissected and controlled with bulldog clamps or slings. The decision to use median cubital, perforating branch or true outflow cephalic vein for the anastomosis will be at the surgeon’s discretion, as will be the decision to create a proximal radial or ulnar–cephalic fistula at the elbow. The size of the arteriotomy will be based on individual patient risks and benefits, but arteriotomies will generally be between 3 and 5 mm in length on the brachial artery and 7–10 mm on the radial artery. An end-to-side anastomosis of vein to artery will be performed with continuous 6.0 (elbow) or 7.0 (wrist) prolene.

### Blinding

Due to the systemic effects of RA (motor blockade, visible venodilatation, etc), which do not occur with LA, it will not be possible to blind the patients, surgical or anaesthetic teams. Dialysis staff and staff performing follow-up visits will be blinded to the intervention. Ultrasound scan (USS) will also provide independent objective assessment of the AVF. The statisticians and health economist will be blinded to the intervention.

### Outcomes

The primary outcome is unassisted functional AVF patency at 1 year, defined as the ability of the AVF to uninterruptedly deliver the prescribed dialysis without intervention.^22^ In predialysis patients, this will be assessed both clinically by an experienced, blinded dialysis nurse and ultrasonographically, the target being 4 mm diameter and access flow being >500 mL/min.^23^

All secondary outcome measures will be assessed at 3 and 12 months. These were chosen with two considerations: patient-centred care and to facilitate health economic analysis. The secondary outcomes reflect the ‘standard CKD set’ recommended by the International Consortium for Health Outcomes Measurement (ICHOM) CKD Working Group.^24^ Key safety and efficacy outcomes for US-guided regional nerve blocks outlined by the National Institute for Health and Clinical Excellence will be recorded.^25^ Secondary outcome measures are listed in box 2. These include access-specific outcomes (eg, reinterventions); patient-specific outcomes (eg, mortality); HRQoL outcomes (eg, KD-QOL); quality and speed of onset of anaesthesia; and safety outcomes.

Box 2Outcome measuresPrimary outcome measureUnassisted functional patency of the index fistula at 1 year.Secondary outcome measuresAccess-specific outcome measuresPatency (ie, is the fistula running ?): defined clinically as the presence of a bruit.Access complications (including infection, stenosis, thrombosis, steal and bleeding).Reoperation/reintervention to maintain or re-establish patency (revisional surgery, angioplasty, stenting or thrombectomy).Alternative accesses (eg, central venous catheters).Time to first cannulation.Cannulation difficulties (including failure to establish two-needle dialysis, infiltration and prolonged bleeding).Patient-specific outcome measuresMortalityDate commenced on HD.Access modality at start of HD.Change of RRT modality.Change of access modality.Access-related hospitalisation.HRQoLEQ-5D-5L (EuroQol)^31^ (crude health status measure and cost-effectiveness analysis).Kidney Disease Quality of Life Short Form^32^ (renal-specific HRQoL).Vascular Access-Specific Quality Of Life^33^ (vascular access-specific HRQoL).AnaesthesiaPain score at incision, at 30 min and 1 hour postoperatively (NRS 0–10).Speed of onset/quality of motor and sensory block.^21^
Need for anaesthetic supplementation.‘Failed block’.Volume of anaesthetic agent (mL).Time to administer anaesthetic (min).OtherChange in surgical plan, for example, switch from brachiocephalic fistula to radiocephalic fistula prior to surgical incision.

